## RESEARCH APPROACH

### B. Research methodology

**Study Location:** The study will be conducted in Hospital Sungai Buloh, Selangor, Malaysia.

**Study Design:** It will be an experimental (randomized Controlled Trial) study design, single-blinded among newly diagnosed HIV positive patients who are eligible to commence ART from December 2013 to August 2014. Following enrollment and allocation to study arm, baseline adherence, clinical symptoms, CD4 count, viral load, Weight, TB status and Opportunistic infection index will be assessed and measured for the 2 groups, prior to the commencement of ART. The intervention group will receive appointment and medication reminders by text-messaging and telephone calls, in addition to standard care. Based on the Theory of Planned Behaviour Model (Ajzen, 1985), appointment reminders will be sent by Short Text Message (in Malay and English languages) three days prior to each individual client's scheduled appointment and telephone call reminders a day prior to the scheduled clinic appointment visits. Weekly short text messages will also be sent to clients to remind them of taking their medications. The control group will only receive standard care and paper-based appointment during clinic visits. Both groups of clients will be followed up for a period of 6 months on ART. Repeated CD4 count, viral load, Weight, TB status and OI index assessment and measurements will be conducted at 3 and 6 months, respectively to determine treatment outcome. Medication adherence will be measured using structured self-report questionnaires. Clinic visits will be measured through medical records of clinic attendance and clinicians' notes.

**Study Duration:** Recruitment and data collection will be from December 2013 to February 2015.

**Study population:** The study population is all HIV positive clients assessed and found to be eligible for ART commencement at Hospital Sungai Buloh, Selangor

**Inclusion criteria:** Age range of 15 to 65 years eligible to commence ART, able to read text messages and have a mobile phone access.

**Exclusion criteria:** Clients who are previously or currently on ART, foreigners & pregnant patients

**Sampling frame:** It is the list of all HIV positive clients assessed and found to be eligible for ART from December 2013 to August 2014 in Hospital Sungai Buloh, Selangor

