**Sampling unit:** Individual patients who are HIV positive but ARV-naïve, assessed and found to be eligible to commence ART based on CD4 < 500 cells/ml and/or WHO stage 3 & 4 disease.

**Sampling method:** A simple random sampling method will be used to select eligible patients for the study.

**Random allocation:** Participants will be allocated to either of the intervention or control groups based on simple, complete randomization technique using their unique ID numbers from a random number table. An independent project biostatistician will generate 1:1 randomization numbers for study arm assignments using a random number generating program. Random allocation will consider and eliminate all forms of possible bias based on the socio-demographic characteristics of the clients.

**Allocation concealment:** Written allocation of assignment will be sealed in individual opaque envelopes marked with study identification numbers which will be available in the study clinic to allocate the target number of participants. After consenting to participate and meeting the inclusion criteria, screened subjects will be enrolled and immediately afterwards are assigned to a randomized study arm by the study coordinator opening the sealed envelopes to determine allocation. Age and gender will be assessed for balance of study arm allocation.

**Blinding:** Investigators will be blinded to intervention assignments.

**Sample size:** The formula for hypothesis testing was used (Lameshow et al., 1990).

$$n = 2d^2[Z_{1-\alpha/2} + Z_{1-\beta}]^2 \mu_1 - \mu_2$$

Where: d = estimated standard deviation (assumed to be equal for each group) is 132 cells/ $\mu$ l (Ref: 10, Table 1)

$\mu_1$  = estimated mean CD4 count increase after commencement of ART with >90% adherence is at least 50cells/ $\mu$ l (14.3%) i.e 550 $\pm$ 50

$\mu_2$  = estimated mean baseline CD4 count at commencement of ART (Based on WHO 2013 guideline of when to commence ART, which is CD4 = 500 cells/ml of blood)

$Z_{1-\alpha/2}$  = standard error when  $\alpha = 0.05$  (95% Confidence Interval) = 1.96

$Z_{1-\beta}$  = standard error associated with power = 0.842 ( $\beta = 0.20$ ) Power ( $1-\beta$ ) = 80%

Expected CD4 increase within 6 months of treatment with >95% adherence is 50 cells/ml

$n = 2 \times (132)^2 [1.96 + 0.842]^2 / (550 - 500)$

$n = 110$  which is the minimum required sample size  $110 + 10\%$  of  $110 = 121$  (attrition)

$121 \times 2 = 242$  (for experimental and control groups)

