Hence, sample size of 121 per group will be used for the study

**Intervention Protocol:** For the intervention group – a ‘reminder module’ will be developed and delivered via SMS and telephone calls by 2 PLHIV (research assistants). This will include weekly SMS medication reminders, SMS reminders 3 days prior to scheduled clinic appointments and telephone call reminders a day prior to scheduled clinic appointment (in addition to standard care – adherence counseling). To ensure confidentiality, typical medication reminder text messages will include a short slogan in Malay language “Apa khabar” “Ini untuk menberithau anda ubat” meaning “How are you?” “This is to remind you of your medications”. Appointment reminder text message would be “Apa khabar” “Tolong ingat tarikh temu janji lusa” meaning “How are you?” “Remember your appointment day after tomorrow” and telephone conversation would be standardized and short, with the message “Apa khabar” “Tolong ingat tarikh temu janji besok” meaning “How are you?” “Remember your appointment tomorrow”. The control group will receive standard care - routine adherence counseling only. Patients will not be required to provide any responses to the text messages. A call and SMS log will be recorded and kept. Two PLHIV that are stable and have been consistent and adherent to ARV medications for at least 2 years will be recruited as research assistants. Using standard training module developed and validated by a team of experts from Universiti Putra Malaysia and Hospital Sungai Buloh, a two-day onsite training of the research assistants on HIV prevention methods, care and treatment issues and how to respond to common questions related to medication adherence, including medication side effects, when asked by study participants, will be conducted. In addition to sending SMS and making telephone calls to patients, they will also be required to provide counseling support and provide guidance to patients (when required) in filling out medication adherence questionnaires during every clinic visits. Patients in the intervention group will be further divided into 2 sub-groups, each under the supervision of one research assistant, who will be responsible for providing them with counseling and psychosocial support, in addition to the care and management provided by the clinicians and nurses, throughout the duration of the study. Each patient in the intervention group would undergo a minimum of three (during clinic visits at month 1, month 3 and month 6) individual counselling sessions with the research assistants lasting an average of 15 minutes per encounter. An intervention manual containing the training modules and implementation guidelines will be provided to the research assistants as spiral-bound hard copy reference document, to guide their interactions with the patient and assure quality and uniformity in the implementation of the intervention.

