| Clinical (Wt, TB & OI status)                   | Clinician's notes       | Clinicians/nurses/adherence counsellors          | Every visit                                       |
| Immunological (CD4)
Virological (viral load) | Laboratory records      | Laboratory scientists                            | Baseline & 6mths                                  |
| Medication adherence                            | Adherence questionnaire | Research assistants/nurses/adherence counsellors | Baseline, then every visit (particularly 3&6mths) |

- **Data Storage:** All data generated from this study will be stored for a maximum of 3 years after the completion of the study, after which they will be destroyed. However, during this period they will remain joint intellectual property of Universiti Putra Malaysia and Hospital Sungai Buloh.

**Primary Outcomes:** The first primary outcome is (improved) patient adherence to ART at six months. This is assessed by self-report using a standardized questionnaire of the number of pills missed in the last 30 days and calculating percent adherence based on the expected number of doses taken and/or number of missed doses. Percent adherence will be analyzed as continuous variable and polytomous variable. Subjects will be considered as "Good adherence" when they achieve an optimal adherence cut of >95% of medications taken as directed with <3 missed doses in the last 30 days period. "Fair adherence" will be considered as 80-95% of medications taken as directed with 3-8 missed doses in the last 30 days period, while "Poor adherence" will be considered as <80% of medications taken as directed with >8 missed doses in the last 30 days period. Medication adherence will be assessed at each follow-up visit, particularly at months 3 and 6. The six month scheduled follow-up is the primary analysis but the three month assessment will allow for evaluating trends but is not the primary outcome.

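### Baseline is assessed after the allocation envelope is opened, so judged and self-reported baseline items can be coloured by knowledge of the arm; the primary outcome definitions are not touched.

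*Protocol*

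**What the plan says.** All references are to the protocol, section B (Research methodology).

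- **Order of steps.** Study Design: "Following enrollment and allocation to study arm, baseline adherence, clinical symptoms, CD4 count, viral load, Weight, TB status" and the opportunistic infection index "will be assessed and measured for the 2 groups, prior to the commencement of ART". Baseline therefore falls between allocation and the start of treatment.
- **Opening the envelope.** Allocation concealment: subjects who have consented and met the criteria are enrolled and "immediately afterwards are assigned to a randomized study arm by the study coordinator opening the sealed envelopes to determine allocation". This paragraph does not mention the baseline assessment.
- **Blinding.** "Investigators will be blinded to intervention assignments". Study Design calls the trial single-blinded. Nothing is said about patients, nurses, counsellors, pharmacists or research assistants.
- **Who delivers and who collects.** Intervention Protocol: the reminder module is "delivered via SMS and telephone calls by 2 PLHIV (research assistants"). The same assistants also help patients with the adherence questionnaires. The table under Data collection gives, for medication adherence, "Research assistants/nurses/adherence counsellors | Baseline, then every visit (particularly 3&6mths"). The text of that section instead names clinicians, nurses and pharmacists for clinical and adherence information.
- **Eligibility.** Sampling unit: patients are "eligible to commence ART based on CD4 < 500 cells/ml and/or WHO stage 3 & 4 disease".

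**The concern.** A baseline taken after randomisation is no longer protected by it. If the patient or the person recording the answer knows the arm, items that rest on judgement or self-report can drift apart between arms before ART or any reminder has had an effect. A comparison of month 6 with that baseline then mixes the effect of the reminders with the drift. A model that adjusts for such an item adjusts for something the allocation may itself have influenced.

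There is also a gap in which a patient can be allocated and leave before giving a baseline. Such a patient belongs to the intention-to-treat population but has no reference value, and would be left out of a complete-case analysis that needs one. Loss of this kind can differ by arm.

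**Working it through.** The question is one of sequence and reach, so the check is to set the paragraphs side by side.

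**1. Is the order really allocation first?** Study Design says so directly. Allocation concealment is consistent with it, because the envelope follows enrolment at once and leaves no interval for baseline work. It does not itself mention baseline, so the order rests on Study Design alone. No other paragraph reverses it.

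**2. Could the arm be known when baseline is taken?** The study coordinator knows it from opening the envelope, but is not listed as a data collector. The more relevant staff are the two research assistants. They deliver the intervention, and the Data collection table lists them for the adherence questionnaire at baseline. The text of that section names other staff, so the protocol is not consistent on who does this. On either reading, no collector outside the word investigators is stated to be blinded. Nothing says the arm is kept from the patient until baseline is complete.

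**3. Which baseline items can that knowledge alter, and where are they used?**

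| Baseline item | Nature | Use in the plan | Exposure |
|---|---|---|---|
| TB status (four categories, one being suspected TB) | clinical judgement | first secondary outcome, compared with baseline | value and missingness |
| Opportunistic infection / WHO stage | clinical judgement | first secondary outcome, compared with baseline | value and missingness |
| Symptom review | self-report | repeated at follow-up; not named in an outcome definition | value and missingness |
| Readiness, stress, alcohol and drug use | self-report | no outcome; possible independent variables in the logistic models | value and missingness |
| Weight | routine nurse measurement | first secondary outcome | mainly missingness |
| CD4, viral load | laboratory records | other secondary outcome | mainly missingness |
| Baseline adherence | self-report, in ART-naive patients | little meaning as a reference for change | slight |

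**4. Do the models carry these items forward?** The Data analysis table gives weight, CD4 and viral load to the t-test and repeated-measures ANOVA. It gives adherence level, TB status, opportunistic infection index and viral suppression to logistic regression with all independent variables, and it names behavioural factors among the independent variables. A questionnaire item taken after allocation can thus enter a model for the categorical form of the first primary outcome. The table does not say whether those models are meant for the arm comparison or for the risk-factor objective.

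**5. Primary outcomes.** Both are six-month measures: percent adherence over the last 30 days, and regularity of attendance. Neither subtracts or refers to a baseline value.

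**6. Sample size.** The plan's figure is reproduced from its own inputs, SD 132, difference 50, two-sided 5% and 80% power: n = 2 × 132² × (1.96 + 0.842)² / 50² = 2 × 17,424 × 7.8512 / 2,500 = 109.4, rounded up to 110 per group. Then 110 × 1.10 = 121 per group, and 2 × 121 = 242. (The printed line divides by 50 rather than 50², which is a separate matter.) The time of baseline does not enter the formula, so re-ordering the steps leaves 121 per group as it is.

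**The case against.** The strongest case on the other side has four parts.

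- **Baseline precedes ART, and neither primary outcome is a change score.** This stands. The unadjusted primary comparisons are unaffected.
- **The outcomes analysed by t-test and repeated-measures ANOVA are laboratory values and a routine weight.** This stands. Knowledge of the arm can hardly move them. A reader might infer that every change from baseline is biased by the whole amount of a baseline shift. The documents do not support that: the additive argument fits unadjusted differences of continuous measures, whereas the judged outcomes, TB status and opportunistic infection index, are categorical and go to logistic regression. The protocol also names the six-month value as the primary analysis for CD4, viral suppression and clinical status.
- **Eligibility already requires CD4 and/or WHO stage, so at least one exists before allocation.** True, but the protocol does not say that this value is the baseline, and it could not stand in for the questionnaire or TB status.
- **Nothing suggests that patients would leave because of their arm.** A reader might attach a percentage to loss between envelope and baseline and call it uneven. The protocol gives no such rate and no sign of imbalance. Selective missingness remains possible but cannot be sized.

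What remains is that judged and self-reported items are collected after allocation with no stated blinding of those who collect them. No other paragraph repairs this.

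**Conclusion.** The point holds in limited form. The sequence is stated plainly and leaves two kinds of data open to knowledge of the arm: TB and opportunistic infection/WHO status, which are compared with baseline in the first secondary outcome, and the self-reported questionnaire items that may serve as covariates. CD4, viral load and weight are exposed essentially through missing baselines only. The definitions of the two primary outcomes are not affected. The one route to a primary outcome is a logistic model of adherence level that includes such covariates.

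No numerical size can be given, since the documents contain no figure for baseline drift or for loss between envelope and baseline. The conclusion assumes that the steps are carried out in the order written, and that the arm is not in fact kept from patients and collectors until baseline is complete; the protocol does not say that it is. This is a worthwhile but lower-priority change.

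**What to change.** Re-order the text in two paragraphs.

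- **Study Design:** place the baseline questionnaire, clinical assessment (symptoms, weight, TB status, opportunistic infection/WHO stage) and blood draw after consent and eligibility, and before allocation.
- **Allocation concealment:** have the coordinator open the envelope only once those steps are recorded as complete, with ART starting afterwards as now. The blood has to be drawn before the envelope is opened; the results need not be back.

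If some item cannot be moved, name the pre-allocation eligibility value as the baseline where one exists (CD4 and/or WHO stage), and have the remaining judged and questionnaire items recorded by staff who do not know the arm. In either case, reconcile the text and table under Data collection on who administers the baseline questionnaire.

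The cost is a few edited sentences and a change of order among steps that all already take place before ART. Sample size, outcomes and analyses stay as they are. A patient who leaves during baseline would then leave before randomisation and could not create a difference between arms.

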The other secondary outcome is (improved) immunologic status/response of patients at six months. This will be assessed based on records of two (2) laboratory measurements – CD4 T cell count and viral load. Patients' CD4 count results at six months will be assessed and compared with baseline values to determine if there's a consistent increase (or otherwise) as expected with strict medication adherence. If patients are adherent to ART regimens, absorb the drugs normally, and if their virus is not resistant to the ART drugs in the regimen, it is expected that their CD4 count should increase from baseline levels by at least 50 cells per microliter of blood within 6-12 months of initiating treatment. CD4 count value at six month scheduled follow-up is the primary analysis.

Similarly, plasma HIV RNA load results at six months will be assessed and compared with baseline levels to determine if there is a significant suppression at six months. If patients are adherent to ART regimens, absorb the drugs normally, and if their virus is not resistant to the ART drugs in the regimen, it is expected that their plasma HIV load should be suppressed to undetectable levels (<400 copies/ml) by six months and remain suppressed thereafter. Analysis of "suppressed" (<400 copies/ml) versus "failure to suppress" (>400 copies/ml) at six months as a dichotomous variable is the primary analysis.

**Data analysis:** Data collected will be collated, checked, cleaned, entered into and analyzed using Statistical Package for Social Sciences software (SPSS) version 21 and AMOS software. Parametric tests (T-test, repeated measures ANOVA) and non-parametric tests will be conducted on the data. P value for test of significance of results will be set at 0.05, alpha level (Type 1 error) at 0.05 (Confidence Interval of 95%), Power at 80% to detect an impact of 15% in the fraction of patients with adherence of at least 90% (assuming a no intervention median adherence level of 90%) using a two-tailed test, Z=1.96, and strength by effect size analysis. Analysis will be by intention-to-treat and complete case analysis.

| Independent variable                                                    | Dependent variable                                                           | Type of analysis                                                           |

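### The 110 per arm rests on the CD4 rise from before to after ART, a secondary outcome, so its 80% power is not power for the randomised comparison; the adherence power claim is not met either

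*Protocol*

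**What the plan says.** All of this is in the protocol, section B, Research methodology.

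- **Sample size.** A two-group formula for means is used, with the SD given as "d = estimated standard deviation (assumed to be equal for each group) is 132 cells" per microlitre. The first mean is CD4 after starting ART with good adherence (550). The second is the "estimated mean baseline CD4 count at commencement of ART" (500). The difference is explained by the line "Expected CD4 increase within 6 months of treatment with >95% adherence is 50 cells/ml". The result is 110 per group, described as a minimum requirement, raised by 10% to 121 and doubled for the two arms.
- **Study Design.** Both arms begin ART and are followed on it for 6 months.
- **Primary Outcomes.** "The first primary outcome is (improved) patient adherence to ART at six months". Good adherence is defined by a cut of more than 95%. The second primary outcome is clinic attendance.
- **Secondary Outcomes.** CD4 belongs here. Of patients who adhere, absorb the drugs normally and carry non-resistant virus, the text says "it is expected that their CD4 count should increase from baseline levels by at least 50 cells per microliter of blood", without regard to arm.
- **Data analysis.** A separate statement claims 80% power for a 15% impact on the fraction with adherence of at least 90%, with a median adherence of 90% without intervention, "using a two-tailed test, Z=1.96, and strength by effect size analysis".

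**The concern.** The formula compares two independent groups, but the two means supplied describe the same kind of patient before and after ART. The control arm also receives ART and adherence counselling, so its CD4 should rise too. The protocol's own assumption of a 90% median adherence without intervention puts about half of the controls at or above the adherence level that the sample-size paragraph links to the 50-cell rise. A 50-cell gap between arms is a different and larger claim than a 50-cell rise, and nothing in the protocol supports it.

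Neither primary outcome enters the calculation that fixes 121 per arm. What is at stake is whether the stated 80% power describes any comparison that the trial is set up to make.

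**Working it through.** **1. The plan's own figure.** The inputs from the sample-size paragraph are SD 132, difference 550 − 500 = 50, z = 1.96 for two-sided 5%, and "standard error associated with power = 0.842".

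n per arm = 2 × SD² × (1.96 + 0.842)² / Δ² = 2 × 132² × 2.802² / 50² = 109.4, rounded up to 110. Then 110 + 11 = 121, and 121 × 2 = 242. The figure reproduces, so the fault lies in what Δ stands for.

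**2. Power for a between-arm CD4 difference.** Power = Φ(Δ / (SD × √(2/n)) − 1.96). With SD 132 and n = 110, the standard error is 132 × √(2/110) = 17.80. The protocol gives no between-arm Δ, so every value below 50 is an assumption.

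| Δ (cells) | Δ / 17.80 − 1.96 | Power, unadjusted | Per arm for 80% |
|---|---|---|---|
| 50 | 0.849 | 80% | 110 |
| 40 | 0.287 | 61% | 171 |
| 25 | −0.555 | 29% | 438 |
| 15 | −1.117 | 13% | 1,216 |

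Adjusting for baseline CD4 would multiply the SD by √(1 − ρ²). The protocol gives no correlation. If ρ is assumed to be 0.5 to 0.7, the SD becomes 114.3 to 94.3. Power is then 37% to 50% for 25 cells and 74% to 88% for 40 cells, and the detectable difference is 43 to 36 cells.

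**3. The adherence statement under Data analysis.** A median of 90% implies that about 50% of controls have adherence of at least 90%. Read as 15 percentage points, the comparison is 50% against 65%, with mean proportion 0.575.

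- Null term: √(2 × 0.575 × 0.425) = 0.6991. Alternative term: √(0.50 × 0.50 + 0.65 × 0.35) = 0.6910.
- n per arm = (1.96 × 0.6991 + 0.842 × 0.6910)² / 0.15² = 169.4, so 170 before any attrition.
- Power with 110: (√110 × 0.15 − 1.3702) / 0.6910 = 0.294, which is about 62%.
- Power with 121: (√121 × 0.15 − 1.3702) / 0.6910 = 0.405, which is about 66%.
- Read as a relative 15% (50% against 57.5%), 693 per arm are needed and 110 give about 20%.

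**4. Dependence on the control rate.** For a 15-point gain with 121 analysed per arm, which means no attrition:

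| Control rate | Power | Per arm for 80% |
|---|---|---|
| 40% | 65% | 173 |
| 50% | 66% | 170 |
| 60% | 70% | 152 |
| 70% | 80% | 121 |

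Of these rates only 70% gives 80% power, and that conflicts with the stated median.

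**The case against.** The best defence has three parts.

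- **The protocol does contain a between-arm power statement on adherence.** This stands. A reader who looks only at the sample-size paragraph might infer that no primary outcome has any power basis, and that would be wrong. But 110 does not come from that statement, 121 per arm do not meet it, and its threshold (at least 90%) is not the primary outcome's cut for good adherence (more than 95%).
- **The CD4 powers below 50 cells are not facts about this trial.** This also stands. A reader might infer that CD4 power is certainly far below 80%. The documents do not support that: they give no between-arm difference, they describe the 50-cell rise as a floor, and baseline adjustment would raise the power. What they do support is that 80% unadjusted requires a full 50-cell gap.
- **Some apparent errors are harmless.** The printed formula lacks the square; taken literally it gives 2 × 132² × 2.802² / 50 = 5,472. A reader might infer that 110 is miscalculated, but 110 uses the square, and the displayed equation may have been damaged in text extraction. Likewise 500 is the CD4 limit for starting ART, not an obvious mean, and patients can also qualify by WHO stage. Only the difference enters n, so the level of 500 changes nothing.

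**Conclusion.** The point holds, and the text is wrong as written. The 110 per arm is correct arithmetic on an effect that is not the randomised contrast, for an outcome that is not primary. Its 80% power carries over to the arms' CD4 comparison only if controls gain 50 cells less than the reminder arm.

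On the protocol's own adherence target the claimed 80% is about 62% with 110 per arm and 66% with 121. This rests on two readings: that the 90% median means a control rate of about 50%, and that 15% means percentage points. The relative reading is worse, at about 20% with 110. For the cut of more than 95% no power can be given, because the protocol states no control rate for it.

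A reader might also infer that the trial must enrol 170 per arm. The documents do not settle that. Enlarging the trial or restating its power are both open to the sponsor.

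**What to change.** 1. Base the sample-size section on the between-arm difference in the first primary outcome at month 6, and state whether the 15% is absolute or relative.
2. Use one adherence threshold in Primary Outcomes and in Data analysis, either more than 95% or at least 90%.
3. In Data analysis, replace the 80% claim with the power that 121 per arm gives over a stated range of control rates, as in step 4 of the working, and show the figure after attrition as well.
4. Stop describing the CD4-based 110 as a minimum requirement.
5. Present CD4 as secondary, with a detectable between-arm difference of about 50 cells (unadjusted, 110 evaluable per arm). If a baseline-adjusted figure is given, state the assumed correlation.
6. Print the squared denominator while the section is open. This is tidying only.

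The cost is a rewritten paragraph and one corrected sentence. The downside is a stated power that looks less favourable. No extra patients are needed unless the sponsor chooses to restore 80%.

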The second primary outcome is (regularity of) scheduled clinic attendance at six months. This will be assessed from records of scheduled clinic visits in the medical records unit and supported by record of scheduled drug pick-up in the pharmacy. Regularity of scheduled clinic visits will be calculated based on number of scheduled clinic visits attended and/or number of times defaulted. Number of missed appointments will be analyzed as a continuous variable and polytomous variable. Subjects will be considered as "Regular clinic attendee" if they never missed any scheduled clinic appointment. A "Defaulter" will be a patient who has missed one or more scheduled clinic appointment for any reason(s), while a patient will be considered "Lost-to-follow-up" if s/he refuses to show up for scheduled clinic visit for 3 consecutive months, after 3 consecutive attempts to track the client and bring them back on treatment. The six month scheduled follow-up is the primary analysis but the three month assessment will allow for evaluating trends.

**Secondary Outcomes:** The first secondary outcome is (improved) clinical status of patients at six months. This will be assessed by measuring their weights, assessing their TB and opportunistic infection status at every clinic visits, particularly at three and six months and comparing these with the baseline status. Patients' weight is routinely measured and recorded by nurses at the study site, as part of standard patient management protocol. These records will be accessed and utilized in the analysis. Patients' TB status is also routinely assessed and recorded by clinicians/nurses/adherence counselors at every clinic visits. These records will be accessed and utilized to categorize patients into four groups, namely "No signs and symptoms of TB", "TB suspected and referred for evaluation", "Currently on INH prophylaxis" and "Currently on TB treatment". Opportunistic infection status will be assessed through WHO clinical staging at every clinic visits. The six month scheduled follow-up is the primary analysis but trend will be evaluated at three months.

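### The appointment SMS is sent three days before the visit, but its text says the visit is two days away, so it names the wrong day

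*Protocol*

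**What the plan says.** The lead time of the appointment SMS is stated twice under Protocol section B, Research methodology. The Study Design paragraph says "appointment reminders will be sent by Short Text Message (in Malay and English languages) three days prior to each individual" client's appointment. The Intervention Protocol paragraph repeats it as "SMS reminders 3 days prior to scheduled clinic appointments".

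The Intervention Protocol paragraph then gives the message itself. The Malay text is "Tolong ingat tarikh temu janji lusa", and the Protocol's own English rendering is "Remember your appointment day after tomorrow". No other appointment SMS text appears in the document, and this one carries no calendar date.

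The second reminder is described in the same paragraph as "telephone call reminders a day prior to scheduled clinic appointment", with a script rendered in English as "Remember your appointment tomorrow".

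The outcome these two reminders serve is set out under Primary Outcomes: "The second primary outcome is (regularity of) scheduled clinic attendance at six months".

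**The concern.** The send day and the wording of the appointment SMS cannot both be right. Three days before a visit, the day after tomorrow is not the day of the visit but the day before it. A research assistant who follows the Protocol exactly would give the patient a wrong date. The call made on that wrong date would then say the visit is the next day, contradicting the SMS.

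Three things are at stake:

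- **The outcome.** The SMS is one of two reminders intended to improve scheduled attendance. Under the Protocol's definitions a single missed appointment, whatever the reason, makes a patient a defaulter, so one confused visit could change a patient's category.
- **The comparison.** Only the intervention arm receives the message, so any harm would tend to weaken the effect under test.
- **Delivery.** Two research assistants each look after a separate sub-group of the intervention arm. Faced with conflicting instructions, one could change the send day and the other the text, and the two sub-groups would then receive different interventions.

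**Working it through.** There is no figure in the plan to reproduce; the check is day arithmetic. Let the scheduled visit be day 0.

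**Inputs**

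| Reminder | When sent (Intervention Protocol) | Day its wording points to |
|---|---|---|
| Appointment SMS | day −3 (also in Study Design) | send day + 2 |
| Telephone call | day −1 | call day + 1 |

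**Day named to the patient = day sent + offset in the wording**

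- SMS: −3 + 2 = day −1. The visit is on day 0, so the error is one day, on the early side.
- Call: −1 + 1 = day 0. Correct.

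**Could a different way of counting remove the gap?** If the visit day itself is counted as day 1, three days prior becomes day −2, and the SMS is right: −2 + 2 = 0. Under the same convention, one day prior becomes day 0, and the call is wrong: 0 + 1 = day +1. No single convention fits both reminders.

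**How many messages?** The Protocol does not state the total number of appointments. The only visits it names for the intervention arm are those at months 1, 3 and 6, where the minimum of three counselling sessions takes place. Assuming one appointment SMS for each of those visits:

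- no dropout: 121 × 3 = 363 messages;
- patients remaining after the planned attrition: (121 − 11) × 3 = 110 × 3 = 330 messages.

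The 330 leaves out any messages sent to the 11 patients before they drop out, and neither count covers visits other than these three. They show how often the error would recur, not how much it would change attendance.

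**Do the two repairs work?**

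- Send on day −2 and keep the text: −2 + 2 = day 0.
- Send on day −3 and have the text say three days: −3 + 3 = day 0. Stating the calendar date works on any send day.

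**The case against.** The discrepancy itself is hard to dispute; the strongest case against the point is about its weight.

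- **It is a small drafting slip, cured by one line.** It touches neither randomisation, outcome definitions, sample size nor analysis. This is true, and the point should not be read as a threat to the trial's validity. It is nonetheless an error in the experimental intervention.
- **The text may be only a sample.** The module and manual are still to be written, and the Study Design paragraph promises messages in both Malay and English. That lowers the risk of the error reaching patients. But the Protocol's word *typical* describes the medication reminders; the appointment text is given as what the message would be, and it is the only one supplied.
- **The harm largely corrects itself.** The SMS errs early, the correct call comes on the very day wrongly named, and patients presumably hold a paper appointment as part of usual care. A patient misdirected to day −1 can still attend on day 0 and need not become a defaulter. This stands, and is why the expected effect is confusion or modest dilution rather than a clear loss of attendance. Any resulting bias would run against the intervention.
- **The message counts look more precise than they are.** This is partly right: the three visits are named for counselling, not as an appointment schedule. The firm figure is one day per message.
- **The three-day rule is probably the intended one, since it appears twice.** That is plausible, but repetition does not prove intent, and either repair is sound.

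**Conclusion.** The concern holds. The send day and the wording of the appointment SMS disagree by one day. Followed as written, each such message names the day before the real visit, in the intervention arm only. Nothing elsewhere in the Protocol corrects it, and the consistent telephone script rules out a counting convention as the explanation.

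The size is one day per appointment SMS. Over the three named visits alone this means 330 messages for the 110 patients remaining after planned attrition, and up to 363 for 121 patients with no dropout, assuming one SMS per visit. The effect on attendance cannot be estimated from the document and is limited by the correct day-before call. This is an inconsistency in the intervention specification, not a fault in the statistical methods. It should be settled before the reminders are used, because it bears directly on a primary outcome.

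**What to change.** Choose one of these:

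1. Keep the text and send the SMS two days before the visit. Change the lead time in both the Study Design and Intervention Protocol paragraphs.
2. Keep the three-day lead time and change the text, in Malay and in English, so that it says the appointment is in three days or, more safely, gives its date. A stated date stays correct even if a message goes out late. Only the Intervention Protocol paragraph changes.

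Carry the agreed version into the reminder module and the intervention manual so that both research assistants work from the same send day and text. The cost is a line of wording, with no change to sample size, visits, outcomes or analysis.
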